#### FMP010/AS01B (Preclinical)

Data from a repeat dose and acute GLP toxicology study (Study No. SVT05-09, Spring [name]) in New Zealand White rabbits indicate that the FMP010/AS01B formulation is safe and immunogenic.

Four groups of rabbits (Groups were Saline alone, AS01B alone, FMP010/Saline and FMP010/AS01B with 10 males and 10 females per group) were evaluated for clinical and pathological evidence of toxicity to FMP010 when administered in combination with AS01B or normal saline. No clinical indications of toxicity were manifest during the course of the study from any of the parameters that were evaluated (BB-IND 13638, Section 5). Thus, the FMP010 when administered alone or formulated with the adjuvant material AS01B was demonstrated to be generally safe and well tolerated.

In this study, the antibody levels in animals immunized with FMP010/AS01B were significantly higher than the antibody levels for any group including for FMP010/Saline at all time points (p<0.001). Even after four vaccinations, the FMP010/Saline group had significantly lower antibody titers than FMP010/AS01B after three vaccinations (third vaccination: 43, 000 versus 191,000 versus fourth vaccination: 39,000 versus 334,000, respectively) (p<0.001).

In a second immunogenicity study performed in rabbits, Spring Valley Laboratories Study ID SVP05-0147, eight New Zealand white rabbits per group were vaccinated at three-week intervals, four times with 50 g doses of FMP010/AS01B and a comparator MSP142 vaccine, FMP1/AS01B (*P. falciparum* MSP142 3D7 allele). Sera were collected two weeks following the third (day 56) vaccination and evaluated by ELISA against homologous and heterologous fragments of MSP142. ELISA antibody titers measured against the FMP010 homologous MSP142 FVO plate antigen for the FMP010/AS01B group were significantly higher then for FMP1/AS01B (ELISA titer is reported as the reciprocal dilution necessary to give an OD=1, FMP010/AS01B and FMP1/AS01B with 188,590 and 63,640 ELISA units, respectively). The FMP010/AS01B heterologous response (i.e. against the MSP142 3D7 allele antigen) was also significantly higher from that induced by FMP1/AS01B (103,571 and 78,573, respectively). Therefore, FMP010/AS01B is highly immunogenic against both homologous and heterologous strain parasites.

When sera from these rabbits were evaluated for their *in vitro* parasite growth inhibitory activities by measuring parasite lactate dehydrogenase levels, pLDH, we observed a statistically significant difference between FMP010/AS01B and FMP1/AS01B induced responses against their respective homologous parasite strains (i.e. FVO and 3D7, respectively), p = 0.06, one-way ANOVA, mean inhibition at 20% serum is 5% for FMP1 and 21% for FMP010.

### FMP1/AS02A

The FMP1 antigen has been under clinical development at WRAIR (30) for over 10 years with accumulated safety and reactogenicity data from two trials conducted at WRAIR and four trials in endemic areas in Mali and Kenya. A Phase 1 dose-escalation study of FMP1/AS02A in 15 malaria-naïve adults conducted at WRAIR in 2001 demonstrated all dose levels to be safe and well tolerated, with no grade 3 adverse reactions and no serious adverse events (31). The vaccine was immunogenic with seroconversion in all vaccinees after the second vaccination. The antibodies induced by this vaccine also demonstrated homologous GIA activity of approximately 15% in 2 of 5 volunteers receiving 50 µg of FMP1 in ASO2A, while there was no demonstrable activity against heterologous (FVO) parasites. Also seen was circumferential staining of fixed schizonts by IFA. A Phase 1/2a study conducted at WRAIR with FMP1/AS02A and RTS,S/AS02A demonstrated that FMP1/AS02A was safe and immunogenic, although it did not confer protection (personal communication [name]).

Of Phase 1 studies conducted in malaria-endemic areas, the first was performed in forty adult participants in Kombewa, Kenya in 2002 comparing FMP1/AS02A to rabies vaccine (32). The most common local side effect related to vaccination with FMP1 was pain which resolved within 48 hrs. No Grade 3 systemic reactions and no vaccine-related vaccine SAE occurred in either group. In adults in Mali, a 50 μg dose of FMP1 in AS02A was safe and well-tolerated with Grade 3 swelling being the most common local side effect as compared to rabies vaccine (33). This swelling lasted less than 48 hours and often was unnoticed by the volunteers.

In Kombewa, Kenya, a Phase I dose-escalation trial of FMP1/AS02A and a rabies comparator vaccine *Imovax*® in children 12-47 months of age was completed in 2003-2004 (33). Safety data showed that the most common solicited adverse events were pain and swelling at the injection site occurring in greater frequency in children who received FMP1/AS02A. These local symptoms had the highest incidence after the first vaccination and resolved within 48-72 hours. Grade 3 local symptoms occurred in less than 10% of children in all dose cohorts. The commonest general symptoms were fever and irritability and these also resolved within 24-48 hours.

### Rationale for this study

The approach to the development of an asexual blood stage vaccine against P. falciparum malaria based upon the MSP1 antigen from the surface of the merozoite is founded on the hypothesis that such a vaccine will elicit strong neutralizing humoral immune responses directed against epitopes located within the 42-kDa carboxy-terminal region of the MSP1 molecule. The main purpose of such a response is to decrease the load of infectious merozoites invading erythrocytes. Indeed, the data available today in the literature suggest these antibody responses targeting the surface of infectious blood stage merozoites are important components of a protective immune response, and that the MSP1 antigen is one of the targets of this response. Ideally, the immune responses should be recalled upon revaccination as well as upon subsequent natural infections. The vaccine should therefore be capable of inducing appropriate subsets of T-helper – memory cells, responding to T-epitopes preferably derived from the MSP1 protein itself.

Prior experience with MSP1-based vaccines in humans has indicated the requirement for sufficiently high antibody titers against epitopes within the carboxy-terminal region of MSP1. In murine and non-human primate models, MSP1-based immunity is strain specific (28). Therefore, it appears that it may be critical to select the most immunogenic allele or a second allele of the MSP1 antigen for inclusion in a malaria vaccine. In addition, molecular typing of P. falciparum parasites from East and West Africa indicate that >90% of the dominant circulating alleles are QKNG and EKNG, and therefore a vaccine that is based on these two allotypes such as the proposed FMP010 stands a better chance of success. This is the compelling justification to proceed with Phase 1a/b clinical testing of the FVO allele of MSP142 (FMP010) proposed in this study (personal communication, [name]).

Given the improved preclinical immunogenicity observed with FMP010, the higher prevalence of the FVO allele circulating in endemic areas, and the improved cell-mediated immune response generated by the adjuvant AS01B (without loss of humoral responses), the opportunity for FMP010/AS01B to provide needed protection against malaria necessitates further evaluation of this allele as a vaccine candidate in both a malaria-naïve and malaria-experienced population. This study is an initial dose-escalation evaluation of the safety and reactogenicity of FMP010/ AS01B at 10 µg and 50 µg of antigen in 0.5 mL of adjuvant in a staggered schedule to permit assessment of safety data at appointed intervals before proceeding to additional vaccinations.

This study will also evaluate immunogenicity of this FMP010/AS01B, and this information will be essential to decision-making policies for consideration of efficacy testing of this candidate. A recently completed Phase 1/2b pediatric vaccine trial with FMP1/AS02A did not appear to demonstrate protective efficacy against malaria in an area of Kenya with multiple MSP-1 alleles (personal communication [name]).

This Phase I clinical study will evaluate the safety, reactogenicity and immunogenicity profiles of FMP010, which is based on the FVO allele of MSP1, formulated with AS01B after intramuscular administration according to a 0-, 1-, and 2-month schedule. Humoral immune responses to MSP1, considered critical for inhibition of parasite growth, will be evaluated at specific time points during the study and compared to humoral immune responses from a previous vaccine trial evaluating FMP1/AS02A in order to evaluate the potential for progression of this vaccine candidate.

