### Analysis of immunogenicity

**Growth Inhibition Assays (GIA)**

Growth inhibition assays (GIA) will be reported in a tabular manner as the percent growth inhibition seen at a given serum dilution compared with the same dilution of pre-immune serum from the same volunteer. GIA will be performed in all volunteers pre- and post-vaccination following standard procedures. An individual serum will be considered to be GIA positive, if compared with paired pre-immune control serum, the growth inhibition value is greater than 20%.

The criteria for FMP010/AS01B progression to Phase 2b and future development are based on establishing statistically significant differences in the ability of the FMP010/AS01B and FMP1/AS02A vaccines to induce biologically relevant antibody responses against homologous parasites *in vitro*. FMP010/AS01B should induce inhibitory antibody responses above the established cutoff level, 20% inhibition (20% serum pLDH GIA assay) in a minimum number of volunteers against homologous parasites, *P. falciparum* FVO (i.e. 10 out 15, thus 67% seropositivity).

| **Criteria** | **FMP010/AS01B** | **FMP1.AS02A** |
| --- | --- | --- |
| Seropositivity | 10 out of 15, 67% | 2 out of 5, 40% |
| Mean Inhibition (%)  Homologous parasites | 30 ± 5 | 15 ± 3 |

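### Progression rests on a significant difference from FMP1/AS02A figures that match a 2001 trial, with no stated re-assay or bridging, and the benchmark does not fit this trial's own >20% positivity rule.

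*Protocol*

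**What the plan says.** Section 1.3.4 (Rationale for this study) sets up the comparison: responses will be "compared to humoral immune responses from a previous vaccine trial evaluating FMP1/AS02A in order to evaluate the potential for progression of this vaccine candidate".

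Section 10.4.3, under Growth Inhibition Assays (GIA), turns it into a decision rule. Progression to Phase 2b is "based on establishing statistically significant differences in the ability of the FMP010/AS01B and FMP1/AS02A vaccines" to induce antibody against homologous parasites. The same section adds an absolute rule: more than 20% inhibition in the 20% serum pLDH assay in at least 10 of 15 volunteers. The criteria table prints seropositivity for the two vaccines as "10 out of 15, 67% | 2 out of 5, 40"%, and mean homologous inhibition as 30 ± 5 for FMP010/AS01B and 15 ± 3 for FMP1/AS02A. The ± is not defined.

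Section 1.3.3 (FMP1/AS02A) shows where the FMP1 column appears to come from. It describes "A Phase 1 dose-escalation study of FMP1/AS02A in 15 malaria-naïve adults conducted at WRAIR in 2001" and reports "homologous GIA activity of approximately 15% in 2 of 5 volunteers receiving 50 µg of FMP1 in ASO2A". No serum concentration or read-out is given for that result.

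Part B has no FMP1 arm. The serology plan in the sample handling section covers this study's sera and allows testing at WRAIR and/or Kisumu. It mentions no archived FMP1 sera, bridging panel or reference serum. The current version is dated 25 March 2009 (Appendix G).

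**The concern.** The FMP1 values belong to another trial, and nothing in the protocol ties their assay runs to the new ones. If the printed figures serve as the comparator, any change in how the GIA reads between the two campaigns is added to the vaccine difference and cannot be separated from it. A two-sample test uses only the spread between volunteers within each group, so its p-value makes no allowance for such a shift. Reading each serum against the same volunteer's pre-immune serum removes shared background, but not a change in assay sensitivity or read-out.

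The benchmark also appears not to have been counted by this trial's rule. A serum is positive here above 20%, whereas the two FMP1 responders are described at about 15% and still enter the table as 40% seropositive.

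At stake is the go/no-go decision for Phase 2b. The co-primary safety endpoints are not affected.

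**Working it through.** **Inputs.** From Section 10.4.3: 10/15 and 2/5; 30 ± 5 and 15 ± 3; cut >20%. From Section 1.3.3: about 15% in 2 of 5 at 50 µg. Assumed, because the protocol does not state them: a two-sided 5% test, normal data, n = 15 against 5 (Group 3 itself is planned at 20, minimum 16), and the size of any campaign drift.

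**1. The plan's figures.** 10/15 = 66.7% and 2/5 = 40.0%, as printed. The FMP1 pair (2 of 5, about 15%) matches Section 1.3.3.

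**2. Which contrast is exposed.** For 10/15 against 2/5, Fisher's exact two-sided p = 0.35; significance would need at least 14/15 (p = 0.032). The planned seropositivity target is therefore not significant in itself, and drift matters mainly for the comparison of means.

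**3. Shift needed for significance.** SE = √(s₁²/15 + s₂²/5), and the critical difference is the Welch t quantile times SE.

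- ± as SD: SE = √(25/15 + 9/5) = 1.86. With about 11.9 degrees of freedom, the critical difference is 4.06 points.
- ± as SE: SE = √(5² + 3²) = 5.83. With about 17.8 degrees of freedom, the critical difference is 12.3 points.
- If 15 ± 3 (as SD) describes only the two responders: SE = √(25/15 + 9/2) = 2.48, and the critical difference is about 11.5 points.

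**4. False significance with equal vaccines.** Both true means are set to 15, and each campaign mean receives an independent normal offset. The last two columns require a significant result favouring FMP010 and also at least 10 of 15 sera above 20%. Rates are simulated; repeat runs agree to about one percentage point.

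| Campaign SD (points, assumed) | Two-sided, ± = SD | Two-sided, ± = SE | Both criteria, ± = SD | Both criteria, ± = SE |
|---|---|---|---|---|
| 1 | 11% | 5% | 0.01% | 1% |
| 2 | 25% | 7% | 0.4% | 1% |
| 3 | 39% | 10% | 2% | 2% |
| 5 | 58% | 19% | 8% | 4% |

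With no drift, the two-sided rate is 5% under either reading.

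**5. The benchmark against the >20% rule.** If FMP1 inhibition were normal with mean 15 and SD 3, the share above 20% would be P(Z > 5/3) = 4.8%, and the chance of 2 or more of 5 would be 2.1%. If ± is an SE, the SD is 3√5 = 6.7, the share is P(Z > 0.745) = 22.8%, and the chance of 2 or more of 5 is 1 − 0.772⁵ − 5(0.228)(0.772⁴) = 32%. The group figures alone therefore do not settle the matter. The direct conflict is in the text: Section 1.3.3 puts those two volunteers at about 15%, which is not above 20%.

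**The case against.** The strongest reply is that the protocol does not rule out a re-run. The secondary objective, in the synopsis and in Section 10.1, speaks of measuring and comparing GIA responses and names both vaccines. Run layout may also sit in a laboratory plan or SAP that is not at hand. This stands: a reader might infer that the FMP1 sera will not be re-assayed, but the documents support only that no re-assay or bridging is stated. What does not need a further document is that the protocol itself fixes the significance criterion and prints the comparator beside it.

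A reader might also infer eight years of assay drift from 2001 and 2009. Those are the year of the earlier trial and the date of this version. When the earlier GIA was run is not stated, and no drift is documented. The own pre-immune control offsets part of any drift.

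Third, the two-sided rates are not false-progression rates. About half of those results favour FMP1, and the 10-of-15 rule makes no use of FMP1 values. Both points stand and are reflected in the last two columns of the table. That protection depends on the assumed common mean of 15, however. With a mean of 20 and SD 5, half the sera exceed the cut, and the responder rule alone is passed 15% of the time without any drift.

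Finally, a re-run is only a partial remedy. Each vaccine is tested on its own homologous strain (FVO or 3D7), the adjuvants differ and, for Part B, so do the populations. This also stands. Antigen and adjuvant belong to the product contrast, but assay campaign is a nuisance that can be removed.

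**Conclusion.** The point holds as a flaw in the progression criterion. It requires significance against five historical volunteers without stating how the assays are linked, and the benchmark's responders fall below this trial's positivity cut. If the printed figures are used, the test's type I error exceeds 5% by an amount the documents cannot fix: about 11% to 58% if ± is an SD and 5% to 19% if it is an SE, for campaign SDs of 1 to 5 points. False progression under both criteria is much lower, about 0.01% to 8% or 1% to 4%. These figures rest on assumed drift, normality, n = 15 against 5, a Welch test and a common true mean of 15. The documents do not support saying that drift has occurred or that a re-run is excluded. The correction is worth making because it affects a go/no-go rule and is cheap; it does not affect participant safety or the co-primary endpoints.

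**What to change.** In Section 10.4.3, and to match in Section 1.3.4, state that any archived FMP1/AS02A 50 µg sera, pre- and post-dose, are re-assayed blinded in the same runs as the FMP010 sera, at the same serum concentration and the same >20% cut, and that only those values enter the comparison.

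If no such sera are available, remove the requirement of statistical significance against FMP1, label that contrast descriptive, correct or annotate the 2/5 figure, and rest progression on the responder criterion measured within this trial.

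In either case, define ± in the criteria table and state that differences in strain, adjuvant and, for Part B, population remain.

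Cost: about 10 extra sera (5 volunteers × 2 time points) in runs already planned, if they exist, which the protocol does not say. Otherwise the change is wording only, and the price is the loss of the FMP1 p-value.

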# STUDY OBJECTIVES AND ENDPOINTS

## OBJECTIVES

# Primary Objective

Assess the safety and reactogenicity of FMP010/AS01B candidate malaria vaccine in healthy malaria-naïve adults from the US and malaria experienced adults in Kenya.

# Secondary Objective

Measure and compare, by Growth Inhibition Assay (GIA), the functional humoral immune responses induced in malaria experienced adults in Kenya to that induced in healthy malaria-naïve adults from the US.

**Tertiary Objectives**

Measure and compare, by enzyme-linked immunoabsorbent assay (ELISA), the humoral immune responses induced by vaccine candidate FMP010/AS01B in malaria experienced adults in Kenya to those induced in healthy malaria-naïve adults from the US.

## ENDPOINTS

**Co-primary endpoints**

- Occurrence and intensity of solicited symptoms on day of vaccination plus days 1, 2, 3 and 7 after each vaccination
- Occurrence and intensity of unsolicited symptoms over a 30-day follow-up period (day of vaccination plus 29 subsequent days) after each vaccination
- Occurrence of serious adverse events (SAEs), defined IAW 21 CFR 312.32(a), during the study period.

**Secondary endpoints**

Functionality of antibodies elicited as measured by percent parasite growth inhibition determined by GIA against the FVO and 3D7 strains of *P.* falciparum at specified time points

**Tertiary endpoints**

Titers of anti-FMP010 and anti-FMP1 antibodies as determined by ELISA at specified time points

- To whole MSP142 3D7 and FVO antigens

● To subunit antigens and selected peptides of MSP142 molecule

**Exploratory Endpoints**

These assays may provide additional information on the immunogenicity of the vaccine candidate FMP010/AS01B. The assays will be completed at USAMRU-K if, after performing endpoint assays, sufficient sample remains and study priorities permit:

- Detection of *P. falciparum* antigens by HRP-2 and pLDH ELISAs
- Titers of anti-FMP010 and FMP1 antibodies as determined by bead-based flow cytometric assays (*Luminex™*) at specified time points
- Anti-merozoite immunofluorescence (IFA) assays to assess ability of antibodies to recognize MSP1 molecule on infected erythrocytes
- Processing inhibition assay (PIA) to assess ability of antibodies to inhibit processing of MSP142 molecule to MSP133 and MSP119
- Cytokine bead-based flow cytometric assay (*Luminex*) to assess cytokine production in responses to vaccine administration
- Assays such as ELISPOT and intracellular cytokine staining to assess cellular immune responses

# STUDY DESIGN OVERVIEW

| **Part B: CONTROLLED DOUBLE BLIND IN WESTERN KENYA** | | | | | | | |
| --- | --- | --- | --- | --- | --- | --- | --- |
| Group | Location | Study Design | Test Article | Volunteers per group | Dose 1 | Dose 2 | Dose 3 |
| 3 | USAMRU-K, Kenya | Controlled Double Blind | Full dose (50 mcg) of FMP010/AS01B | 20 | **Part B Day 0** | **Part B Day 28** | **Part B Day 56** |
| 4 | USAMRU-K, Kenya | Controlled Double Blind | Rabipur® Rabies Vaccine | 10 | **Part B Day 0** | **Part B Day 28** | **Part B Day 56** |

**Study Initiation**

Vaccination and review of the safety data for Groups 1 and 2 (Part A in the USA) will occur before vaccination can begin in Part B (Kisumu, Kenya). Safety data for Groups 1 and 2 (Part A in the USA) will be collected and submitted to a Safety Monitoring Committee (SMC) for recommendations about progression to Part B in Kisumu, Kenya. If progression to Part B is recommended the safety data will be presented to the Medical Monitor for Part B and the KEMRI Ethical Review Committee for evaluation and recommendation to initiate Part B of the study.

Duration of the study, per subject is approximately seven months (screening, enrollment, vaccination, and follow-up). All subjects will be followed for safety for a period that extends to two months post Dose 3. Any data collected after the final analysis will be reported in an annex report. Data collection will be by conventional CRF.

**Part B: Phase 1b Double-blind Controlled at USAMRU-K in Western Kenya**

- Healthy, malaria-experienced adults aged 18-50 years
- Two groups (20 volunteers in Group3, 10 volunteers in Group 4; 30 volunteers total)
  - Group3 will receive full dose FMP010 antigen (approximately 50 µg) in 0.5 mL AS01B adjuvant
  - Group 4 will receive full dose rabies vaccine (Rabipur®)
- Vaccination schedule of 0, 28 ± 3days and 56 days ± 3 days
- Intramuscular route of administration in the deltoid muscle of the non-dominant arm

# STUDY COHORT

## Number of subjects / centers

**USAMRU-K Phase**

Up to 30 healthy, malaria-exposed adults aged 18-50 years will be enrolled in Part B of the study. Part B will be performed at Muriithi-Wellde Clinical Research Center (CTC), Western Kenya. The population of Kombewa Division is primarily Luo. The majority of the population speaks both Dholuo and Kiswahili.

The sample size for both Parts was chosen to assess the first-in-human experimental vaccine, FMP010/AS01B, in small numbers of volunteers and is consistent in size with a Phase 1 study of FMP1/AS02A (3D7 allele) carried out previously at WRAIR.

## Inclusion criteria

- A male or non-lactating female 18 to 50 years of age (inclusive) at the time of screening
- Free of significant health problems as established by medical history and clinical examination before entering into the study
- Available to participate for duration of study (approximately seven months)

If the subject is female, she must be of non-childbearing potential (either surgically sterilized or one year post-menopausal) or, if of childbearing potential, she must have a negative pregnancy test at the time of vaccination, be capable of preventing pregnancy for at least one month prior to determination of eligibility (to include abstinence or contraceptives (for example intrauterine contraceptive device; oral contraceptives; Norplant® or Depo-Provera® ), and must agree to continue such precautions for two months after completion of the vaccination series.

- Written informed consent must be obtained from the subject before screening procedures.
- After the group briefing, volunteers will review the protocol, one-on-one, with a member of the study staff to ensure they understand the study and consent document. Clinical points of the study will be reviewed again during the screening evaluation.

